### Study design and participating sites

The prospective, observational study will be conducted following a resident-led model, similar to what has been described by Banghu et al. and van Rossem et al. and the SPIRIT guidelines (23–25). Briefly, teams of medical students and surgical residents with senior staff surgeon oversight collect data on patients across Italy for 18 months. The Data Coordination Center (DCC) is the Colorectal Surgery Unit of Surgery Centre, – Fondazione Campus Bio-Medico University Hospital, University Campus Bio-Medico of Rome, Italy and the Study Director is responsible for the selection of the study sites. Any center performing emergency surgery can participate in this trial. The centers include academic medical centers, teaching hospitals, tertiary referral centers and community hospitals. Although this study protocol is similar to what adopted in previous research (26), in order to ensure that there is a uniformity of data acquisition, centers which do not participated in such previous study performed a 3-month pilot study collecting data retrospectively. All the data taken refers to the time of access of the patient in the emergency room or in any case to the first data available before any procedure. Such data are not published, and are stored separately for possible further analyses. All patients are treated according to the local hospital protocol and receive routine care as standard therapy. Whenever possible, patients with intestinal obstruction are treated according to SICUT Delphi consensus statements (27). The duration of the recruitment phase of patients is expected to be 18 months. The main strength of this project is the multicenter, prospective, contemporary methodology, with independent validation of data. This will produce high quality data on the emergency procedures carried out for gastro-intestinal emergency and on outcomes throughout Italy from a wide range of hospital types. Limitations include the inability to assess the postoperative visits to the general practitioner. Moreover, a minority of patients may present to other hospitals with complications following surgery, or because they need medical assessment. Despite this, teams will try to document the number of patients that were readmitted to other facilities. Our study uses the standard 30-day follow-up period, as this is the international standard and allows comparison to other studies. However, complications which may occur after 90 days will be reported as completely as possible.

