### Outcome measures

The primary outcomes are 30-day overall postoperative morbidity and mortality rates. Secondary outcomes are 30-day postoperative morbidity and mortality rates, stratified for each procedure or cause of intervention, length of hospital stay, admission and length of stay in ICU, and place of discharge (home or rehabilitation or care facility). Severity of every disease will be assessed according to the AAST EGS score (29). Other secondary outcomes include the number of elderly subjects undergoing yearly emergency surgery, reported as the elderly to non-elderly patient ratio, emergency surgery in the elderly per 100,000 inhabitants, frequency of use of frailty score. Elderly are define as any patient >65 years old according to the World Health Organization. Moreover, the study will evaluate the sensitivity and specificity of the following scores: Charlson Age Comorbidity Index (CACI), Simplified Acute Physiology Score II (SAPSII), American College of Surgeons National Surgical Quality Improvement Program (ACS NSQIP), Calculation of Postoperative Risk in Emergency Surgery (CORES), Surgical Mortality Probability Model (SMPM), Urgent Surgery Elderly Mortality (USEM) score, Emergency Surgery Frailty index (EmSFI), 5 modified Frailty Index (5-mFI). The postoperative complications are reported and categorized according to the Clavien-Dindo classification system. Morbidity we will be assessed by detecting all adverse event according “Common terminology criteria for adverse events version 5” (30). Therefore, the Comprehensive Complication Index will be calculated (31).

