### Data collection, validation, and management

In each participating hospital, one local investigator (usually a surgical resident/student) is responsible for data collection and for entering data into a password-protected electronic spreadsheet specifically constructed with predefined data fields. There are six categories, namely “patient demographics”, “comorbidities”, “clinicopathological data”, “surgical intervention”, “score”, and “follow-ups” (Table 1). Patient details will be recorded and anonymized using the code centre, an ID number and a unique alphanumeric code for any further integration. The anonymization procedure is provided by the enrolling centre. Patient data will be collected, if possible, on a daily basis; preoperative and intraoperative data will be processed after surgery, and the postoperative outcomes will be noted at the time of discharge and at the end of follow-ups. Data will be obtained from the electronic patient database, from admission charts, and operative reports, or directly from the surgeon who performed the operation when details were unclear or missing. Consent to participate in the study and to collect data for scientific purpose will be obtained from the patient at admission. The standardized data collection protocol has been approved by the Central Ethical Committee. There is no minimum number of patients per centre. Following data collection, only datasets with >95% data completeness will be accepted for pooled national analysis. The principal investigator (PI) at the selected site will identify an independent assessor to validate all data, with a target of >98% accuracy. Overall, at least 5% of the datasets will be independently validated. Outcome data will not be analyzed specific to each individual center. Data will be submitted monthly *via* e-mail or inserted in an online module. Once in the Data Coordination Centre (DCC) pooled warehouse, records are reviewed and edited and, whenever necessary, transformed to comply with the GESEMM data dictionary (see Table 1 for further information). The Study Director and the Study Coordinator will then identify unacceptable data entries using custom software queries to detect missing, impossible and improbable values and logical inconsistencies between data fields and across the forms. The DCC will then ask the sites to check for the incomplete data, and once the sites have resolved the data queries, the DCC will update the patient records. To identify complications during follow-up, each center will check their database to monitor visits to the emergency department, postoperative imaging or intervention, outpatient visits or hospital readmissions. Additional checking of admission diagnosis and surgical procedures in the study months will identify any missing patients. The data will be collected from each individual center according to the current Italian Law regarding privacy policy (Legislative Decree no. 196/2003 “RIGHT TO PERSONAL DATA PROTECTION CODE”). It will be the responsibility of the local investigators to ensure that the local data will be protected and held according to such privacy policy and in line with what has been approved by the ethics board. No patients are involved in setting the research question or the outcome measures; nor are they involved in the design and implementation of the study. There are no plans to involve patients in dissemination of results.

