	Onset symptoms	Obstruction, acute abdomen (peritonitis—abscess and/or overt perforations), Vascular disorders, Trauma
	Primary operative indication	Benign/malignant/delayed elective
	Surgical approach	Open/Laparoscopic/Laparoscopic converted/Laparoscopic assisted
	Primary surgical procedure	ICD-9-CM code
	Associated procedures	Numbers
	List of associated procedures	ICD-9-CM code
	Intraoperative reliefs	Blood loss (ml), peritoneal contamination (yes/no)
	Operative time	Minutes
	ICU admission	Yes/no
	ICU length of stay	Dayes
Follow-ups	Date of discharge	Day/month/year
	Total length of stay	Days
	Type of discharge	Home, short-term rehabilitation facility, caregiver residential facility
	Complications 30-daypostoperatively	Yes/no
	Complication type	Free text
	Complication grade (Clavien-Dindo classification)	None/I/II/III/IV/V
	30-day mortality	Yes/no
Score		ASA, CACI, SAPSII, ACS-NSQIP, CORES, SMPM, USEM, EmSFI, 5-mFI

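### The discharge options are not exhaustive: a patient moved directly to another acute hospital has no correct code, so place of discharge will be miscoded or selectively missing for those patients

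*Protocol article*

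**What the plan says.** In the protocol article, the Follow-ups form of Table 1 gives Type of discharge three options: "Home, short-term rehabilitation facility, caregiver residential facility". Outcome measures lists, among the secondary outcomes, "place of discharge (home or rehabilitation or care facility"), which is the same set. It also lists "length of hospital stay, admission and length of stay in ICU", and Expected results promises mean hospital stay by surgical procedure group.

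On who takes part, Study design and participating sites says: "The centers include academic medical centers, teaching hospitals, tertiary referral centers and community hospitals".

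On how entries are handled, Data collection, validation, and management says that data go into a "password-protected electronic spreadsheet specifically constructed with predefined data fields", that records at the coordinating centre are, where needed, "transformed to comply with the GESEMM data dictionary" (with a pointer to Table 1), and that "only datasets with >95% data completeness will be accepted for pooled national analysis". Missing or inconsistent entries are queried back to the sites.

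The only text on care at other hospitals, in Study design and participating sites, concerns patients who present or are readmitted elsewhere after surgery. It does not cover direct transfer.

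**The concern.** A categorical outcome needs options that cover every patient it applies to. Here one foreseeable destination is absent both from the form and from the definition of the outcome. A site that has moved a patient to another acute hospital can enter a destination that is not true or leave the field empty.

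Place of discharge is a stated secondary outcome, so either choice affects a result the study intends to report. The missing code is also the only place in Table 1 where a transfer could have shown up. Without it, an analyst cannot tell which recorded stays ended in transfer, and cannot check whether mean stay for a given procedure depends on them.

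**Working it through.** No figure in the plan needs reproducing. The check sets the printed fields against the outcome definitions and the data-handling rules.

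1. **Is the list closed?** Table 1 prints three destinations and no residual code. The same table does print a residual code elsewhere: the organ category on the Surgical intervention form ends with one. Outcome measures repeats the three destinations. Two places agree, so this is not a slip in one table cell.

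2. **Is the missing destination foreseeable?** The network includes community hospitals and tertiary referral centres, and any centre that performs emergency surgery may join. Direct transfers between acute hospitals are plausible in such a network. No rate is given.

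3. **Would the queries repair it?** A query returns the record to the site, but the answer must still fit the dictionary, and the dictionary lacks the true answer.

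4. **Would the completeness rule catch it?** The article does not define a dataset. Suppose it means one patient's record, and count only the printed rows of Table 1: 9 demographic, 3 clinicopathological, 2 comorbidity, 11 surgical, 7 follow-up and 1 score row, or 33 in all. One blank leaves 32/33 = 97.0%, above the 95% threshold. Counting the items inside each row separately would bring it closer to 100%. A blank in this field alone therefore passes.

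5. **What happens to the reported percentages?** Let *p* be the share of discharged patients who were transferred.
   - If all are coded to one of the three destinations, that category is too high by *p*.
   - If all are left blank and dropped, the three categories are taken over a share 1 − *p* of patients, so each is inflated by the factor 1/(1 − *p*), and transfers do not appear at all.
   - Purely as an assumption, with *p* = 1%, 3% or 5% the factor is 1/0.99 = 1.010, 1/0.97 = 1.031 or 1/0.95 = 1.053. None of these values of *p* comes from the documents.

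6. **What about length of stay?** "Total length of stay" is a separate field in days, and ICU stay is on another form. The article gives neither a counting rule at transfer. The missing code does not change the recorded days. It does remove the means of identifying transferred patients when mean stay per procedure is tabulated.

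**The case against.** The strongest defence is that this is a condensed article and the option list may be shorthand for live discharges. It also has no code for in-hospital death, which is captured separately through 30-day mortality and Clavien-Dindo grade V. The list may be fuller in the working spreadsheet. That is possible, but the article presents Table 1 as the data dictionary and repeats the same three destinations in the outcome definition, so as written the gap stands.

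It is also fair to say that a wrong code is not inevitable, because a site may leave the field blank. That stands, but it only replaces a false destination with a value missing for transferred patients in particular.

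A reader might infer more than the documents support:

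- **That hospital and ICU stay are cut at the transfer date.** No section says so. The stay fields have no printed end point and are not tied to the discharge code. A counting rule may sit in the full protocol.
- **That one episode is counted as two short stays.** Inclusion requires urgent or emergency abdominal surgery. A second record would need a second eligible operation at another participating centre, and the exclusion of inpatients already scheduled for the same procedure narrows this further. Transfer for postoperative care alone creates no second record.
- **That community hospitals are unevenly affected.** The article says outcomes will not be analysed by centre and plans no comparison by hospital type.
- **That mean stay is understated by a stated percentage.** One could assume 8 days for patients not transferred, and 20 true but 4 recorded days for those transferred. At 1% to 5% transferred, the recorded mean would be 7.96 to 7.80 days against a true 8.12 to 8.60, or about 2% to 9% too low. Every input is invented and truncation itself is not established, so this is not an estimate. The Statistical analysis section also allows medians, which would move little.

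**Conclusion.** The point holds in a limited form. The discharge options, in both Table 1 and the outcome definition, omit direct transfer to another acute hospital. Place of discharge will be wrong or selectively missing for every patient so transferred. Their stays cannot be identified when mean length of stay per procedure is reported.

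The conclusion rests on two things: that the printed list is the operative one, and that at least some transfers occur, which the mix of centres makes likely but does not quantify. The size is unknown and cannot be derived from the documents. The effect is confined to secondary, descriptive outcomes; 30-day morbidity and mortality do not use the field. The change is worth making because it is small and corrects a stated outcome.

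**What to change.** - Add transfer to another acute hospital, with its date, to Type of discharge in Table 1 and to the place-of-discharge definition in Outcome measures. Report it as its own category.
- State that length of stay is the stay at the enrolling hospital. Show mean stay per procedure group with and without transferred patients.

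This takes one code, one date and one or two sentences. Following a patient's stay across hospitals is not needed and would be costly, since the receiving hospital may be outside the study. Treating stay as censored at transfer is a debatable analysis choice and is not needed either.

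The downside is that sites must recheck the discharge code of patients already entered. The retained patient codes, the query process and the time-line stage for completing missing data provide a route for this.

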### Study time-line

The following timeline has been outlined, to define specific stages of the study:
•May 13–June 30, 2021: invitation to satellite centers to participate.•1 July–31 August, 2021: pilot study and standardization of data collection.•1 September 2021–31 August, 2022: main data collection.•1 September 2022–28 February, 2023: data collection on specific topics.•1 March–30 June, 2023: completion of the collection of any missing data.•1 July–31 December 2023: “interim analysis” of complete data excluding follow-up•February 28, 2025: study completion for last potential follow-up.

### Statistical analysis

The report of this study will be prepared in accordance with guidelines set by the STROBE (Strengthening the Reporting of Observational Studies in Epidemiology) statement for observational studies (30). Statistical analysis will be performed either with SPSS software, version 21 to 26 (IBM Corp. Released 2020. IBM SPSS Statistics for MacOsx, Version 27.0. Armonk, NY: IBM Corp) for MacOSX or StataCorp2019 STATA Statistical Software: release 16 (College Station,TX: StataCorp LLC). First, data normality will be tested using the Shapiro–Wilk test or Kolmogorov– Smirnov test. Dichotomous data and counts will be presented in frequencies. Continuous data will be presented as mean values plus standard deviations, or as median values and interquartile ranges. The 95% confidence interval will always be reported where appropriate. Differences between means will be compared using the independent sample Student's *t* test, the pairwise comparison Student's *t* test, the Mann–Whitney *U* test, the Kruskal–Wallis test or other analysis of variance (ANOVA) tests. Differences between medians will be compared using the Kolmogorov–Smirnov test or special application of the Pearson chi square test by using the median as cut-off. To compare differences in frequencies, Fisher's exact test or *χ*^2^ test, with or without Yates correction will be performed. Receiver operating characteristic (ROC) curve analysis will be performed to estimate sensitivity and specificity of each score. Linear correlation will be assessed by Pearson's or Spearman's test, if needed. Multivariate analyses will be performed using logistic regression models that consider mortality and morbidity as dependent variables. A *P* value of <0.05 will be considered statistically significant.

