
## Trial population recruitment and eligibility criteria

### Inclusion criteria

All patients over the age of 18, undergoing urgent/emergency abdominal surgery will be included in the study. Emergency procedures are defined as unforeseen, non-elective operations according to the NCEPOD Classification of Interventions (28). The type of surgical approach takes into account open abdominal or laparoscopic procedures, including laparoscopic procedures that are converted to open abdominal procedures. Surgical procedures will be sorted on the basis of the 9th revision of International Classification of Disease Clinical Modification (ICD-9-CM). All abdominal procedures with ICD-9-CM code numbers ranging from 42.0 to 54.99 are considered eligible.

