### Expected results

We expect to obtain the following results:
•Identification of the mortality rate at 30 days (30-day mortality rate), divided according to the different type of intervention (ICD-9-CM classification) and stratified for 5-years age group;•Identification of the general morbidity index at 30 days (30-day morbidity rate), divided according to the different type of intervention (ICD-9-CM classification) and stratified for 10-years age group;•Identification of mean length of hospital stay (LOS), in days, according to the different surgical procedure group (ICD-9-CM classification);•Sensitivity and specificity of the following scores:
- Charlson Age Comorbidity Index (CACI)- Cohomprensive Complication Index- Simplified Acute Physiology Score II (SAPSII)- American College of Surgeons National Surgical Quality Improvement Program (ACS NSQIP)surgical risk calculator- Calculation of postOperative Risk in Emergency Surgery (CORES)- Surgical Mortality Probability Model (SMPM)•Evaluation of the prevalence of emergency surgery in different age groups by geographic area (Emergency surgery per 100.000 inhabitants);•Identification of an Elderly / Non Elderly ratio;•Evaluation of the use of the following scores in elderly patients:
- Frailty Fried Index- Canadian Study of Health and Aging (CSHA) frailty score- Emergency Surgery Frailty Index (EmSFI)- Urgent Surgery Elderly Mortality (USEM) score- 5 modified Frailty Index (5-mFI)

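### Student's pooled-variance t test is the only two-mean test named for independent groups, and it can miscalibrate comparisons between groups that differ in both size and spread

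*Protocol article*

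**What the plan says.** The Statistical analysis section starts with a distributional check: "First, data normality will be tested using the Shapiro–Wilk test or Kolmogorov– Smirnov test". Summaries follow either form: "Continuous data will be presented as mean values plus standard deviations, or as median values and interquartile ranges". For inference on means it states "Differences between means will be compared using the independent sample Student's" t test. The same sentence adds a pairwise t test, Mann–Whitney and Kruskal–Wallis, and closes with "test or other analysis of variance (ANOVA) tests". The threshold is a P "value of <0.05 will be considered statistically significant". No unequal-variance form and no check of variances is mentioned, and no rule links the normality result, or any outcome, to a particular test.

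The groups available for comparison are broad. Under Inclusion criteria, "All abdominal procedures with ICD-9-CM code numbers ranging from 42.0 to 54.99 are considered eligible", and Table 1 sorts operations into organ categories that include appendicitis, large bowel, oesophagus and solid organs. Length of hospital stay and of ICU stay are secondary outcomes. Expected results promises "Identification of mean length of hospital stay (LOS), in days, according to the different surgical procedure group (ICD-9-CM classification"). The primary outcomes are binary: "The primary outcomes are 30-day overall postoperative morbidity and mortality rates".

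**The concern.** Student's independent-sample test estimates one common variance for both groups. That is harmless if the groups have equal variances, or if they are of equal size. Nothing in this design provides either condition: patients are neither randomised nor matched, and group membership follows from the disease and the operation. The Discussion itself sets out to report which procedures account for most cases, which presupposes unequal counts.

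If the smaller group is the more variable one, as might be so for an uncommon high-risk operation set against a common low-risk one, the pooled standard error is too small: differences are declared too often and the interval is too narrow. If the larger group is the more variable one, the error reverses and real differences are missed. A normality check does not detect either situation, because it says nothing about whether the variances are equal.

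**Working it through.** The article states no sample size, group size, SD or target difference for any continuous outcome, so there is no figure to reproduce. Everything below rests on assumed inputs, shown as a range, with a two-sided 5% level (the sidedness is also an assumption).

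**Formula.** For group sizes n1, n2 and SDs s1, s2, with shares f1 = n1/(n1+n2) and f2 = n2/(n1+n2):

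- variance used by Student's test: Vp = (f1·s1² + f2·s2²)(1/n1 + 1/n2)
- true variance of the mean difference: Vt = s1²/n1 + s2²/n2
- large-sample type I error = 2·(1 − Φ(1.96·r)), where r = √(Vp/Vt). r is also the interval width relative to the correct width.

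Multiplying both group sizes by the same factor leaves r unchanged, so a larger cohort does not remove the error. If n1 = n2 or s1 = s2, then r = 1 and the error is 5%.

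**Example, small group more variable.** 900 patients with SD 4 days and 100 with SD 8 days:

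- Vp = (0.9×16 + 0.1×64)(1/900 + 1/100) = 20.8 × 0.01111 = 0.2311
- Vt = 16/900 + 64/100 = 0.6578
- r = √(0.2311/0.6578) = 0.593; 1.96 × 0.593 = 1.162; type I error about 24.5%. The nominal 95% interval therefore covers about 75%.

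**Example reversed, large group more variable.** 900 with SD 8 and 100 with SD 4:

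- Vp = (0.9×64 + 0.1×16) × 0.01111 = 59.2 × 0.01111 = 0.6578; Vt = 64/900 + 16/100 = 0.2311
- r = 1.687; 1.96 × 1.687 = 3.307; type I error about 0.1%
- power for a true difference of 1.35 days: true standard error √0.2311 = 0.481, and 1.35/0.481 = 2.81. Student: Φ(2.81 − 3.31), about 31%. Welch: Φ(2.81 − 1.96), about 80%.

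**Range** (n − 1 weights, which move the 900/100 figure from 24.5% to 24.6%; relative interval width in brackets):

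| Split | SD ratio | Small group more variable | Large group more variable |
|---|---|---|---|
| 500/500 | 2 | 5.0% (1.00) | 5.0% (1.00) |
| 900/100 | 1 | 5.0% (1.00) | 5.0% (1.00) |
| 667/333 | 1.5 | 8.5% (0.88) | 2.6% (1.14) |
| 800/200 | 1.5 | 12.1% (0.79) | 1.3% (1.27) |
| 800/200 | 2 | 17.9% (0.69) | 0.4% (1.46) |
| 900/100 | 1.5 | 15.4% (0.73) | 0.7% (1.37) |
| 900/100 | 2 | 24.6% (0.59) | 0.1% (1.69) |

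**Simulation check** (4,000 data sets per setting). With normal data, Student's test rejected a true null in 17.6% and 0.4% of runs at 800/200 with SD ratio 2 (small and large group more variable), and in 24.5% and 0.1% at 900/100. Welch's test stayed between 4.2% and 5.5% in every normal setting. With lognormal data Welch gave 4.8% to 8.5%; the 8.5% arose at 900/100 with the small group more variable, where Student gave 23.2%.

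**More than two groups.** With normal data and sizes 400/300/200/100, equal-variance ANOVA gave 17.7% for SDs 4/6/8/12 and 2.3% for SDs 12/8/6/4. Welch's ANOVA gave 4.9% and 5.4%.

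**Would length of stay reach Student's test?** For an assumed skewed stay (lognormal, mean 8, SD 6 days), Shapiro–Wilk rejected normality in 98.6% of samples of 50 and in all samples of 100. If that sends stay to a rank test, the question changes: with equal means of 8 and lognormal SDs of 6 and 12, in either order, Mann–Whitney rejected in 93% to 100% of runs (1,000 per setting).

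**The case against.** The strongest reply is that Student's t is one item on a menu. A normality test comes first and rank tests stand in the same sentence, so skewed length of stay would probably never be given to Student's test. That stands. A reader might infer from the table that the plan's P values for length of stay will be wrong by these amounts. The article does not support this: it assigns no test to stay, Expected results promises only a descriptive mean per procedure group, and the sizes and SDs above are assumptions. The diversion is only a partial rescue, though. No rule says which test follows a failed normality check. Variables that pass it, perhaps some laboratory values or operative time, are exactly those left to Student's test. And the rank tests do not compare means, nor do they give an interval for a difference in mean stay.

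Two further limits also stand. A reader might infer that equal-variance ANOVA is fixed, but the open wording about other ANOVA tests does not exclude Welch's. The pairwise t test may be a paired test, which pools no group variances and is unaffected.

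It can also be said that the variance form is a detail for an analysis plan that is not shown. That carries less weight, because the article names a specific test, and under its usual meaning that test is the pooled one.

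**Conclusion.** The point holds in a limited form. The independent-sample test named for two means pools variances, and no unequal-variance alternative is stated, in a cohort whose natural groups are likely to differ in size and spread. Any mean comparison that does use this test can be miscalibrated in either direction: about 0.1% to 25% type I error for splits up to 90/10 and SD ratios up to 2, and 5% if sizes or SDs are equal. The true imbalance is unknown, so the text supports only that results can be wrong, not that they will be.

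The reach is confined to secondary or descriptive comparisons of continuous variables such as stay, operative time and laboratory values. The 30-day morbidity and mortality rates, the ROC analyses and the logistic models do not depend on it. Severity is minor.

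**What to change.** In the Statistical analysis section:

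- replace the independent-sample Student's test with Welch's t test as the default for two means, without a preliminary test of equal variances;
- state that the ANOVA used for more than two groups is Welch's;
- report mean differences with unequal-variance 95% intervals, and use bootstrap intervals where stay is strongly skewed and groups are small, since Welch is then only approximate;
- leave any paired t test as it is.

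The cost is one sentence, with a negligible loss of power if the variances turn out equal.
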